### Process evaluation

*Recruitment* Participants for the process evaluation are healthcare professionals located in the region of Muensterland, Tecklenburger Land and Osnabrueck, Germany (n = 30 neurologists and n = 150 therapists). All healthcare professionals are given access to JamesAKTIV and are invited for the quantitative process evaluation (i.e., social network analysis survey and the team effectiveness survey) via email for participation in the online survey. For the qualitative process evaluation (i.e., interviews and focus groups), a purposive sample will be drawn from all participating ParkinsonAKTIV healthcare professionals.

*Social network and team effectiveness analysis* A quantitative social network and team effectiveness analysis is performed using an online survey to analyze patterns of relationships among stakeholders within the system and to map the connection and provide insights into communication and collaboration between project partners. Another part of the online survey includes 25 questions on perceived team effectiveness, which cover aspects about psychosocial team characteristics and norms, dynamics and processes, such as communication, decision-making and potential conflicts within the team, and team outcomes [17].

*Interviews and focus groups* For semi-structured interviews, approximately, 10 – 15 healthcare professionals from ParkinsonAKTIV are approached and asked to participate in telephone interviews. The interviews aim to shed light on factors such as the acceptance of ParkinsonAKTIV (i.e., JamesAKTIV) for routine care implementation, willingness to work with JamesAKTIV, as well as its barriers and facilitators. In addition, focus groups with participating healthcare professionals are conducted to investigate interdisciplinary communication between different healthcare professionals and to gain insights into the quality of network interactions.

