### Effectiveness evaluation

*Recruitment of intervention group* Recruitment of PwP takes place during face-to-face consultations by their treating neurologists where further information about ParkinsonAKTIV is provided. Until the caseload is reached, all new patients that fulfil the inclusion criteria, will be enrolled into the intervention arm. Additional information about the procedure for participation is available on the PNM+ website as well as flyers.

*Recruitment of control group* To compare the treatment of PwP in ParkinsonAKTIV with standard care, members of a nationwide support group for PD, the Deutsche Parkinson Vereinigung e. V. (dPV), are approached for study participation through their member’s journal. The dPV member pool will be approached twice for participation in the survey, once for the baseline survey and once at the end of the study.

Patients eligible for the intervention arm must fulfill the following inclusion and exclusion criteria:

*Inclusion criteria*
Primary PD according to the international classification (ICD 10 G20.x)Age of ≥ 30 yearsExisting medical treatmentPD care must be fully provided in the region Muensterland, Tecklenburger Land and the district and city of Osnabrueck

*Exclusion criteria*
Secondary PDInsufficient knowledge of the German languageIntellectually and linguistically unable to answer the questionnaires

*Data collection* For the effectiveness evaluation and the health economic evaluation, quantitative data will be collected via paper–pencil surveys among PD patients (i.e., primary outcome: health-related quality of life and secondary outcomes: patient-reported healthcare costs, see Table 1). In addition, neurologists assess disease specific measures during their face-to-face consultations (i.e., secondary outcomes: disease severity and PD symptom severity, see Table 1).

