*Sample size calculation* The sample size calculation is based on the primary outcome, quality of life. According to a-priori power calculation, based on an independent t-test and an effect size of d = 0.3 [3, 11]. With an alpha of 0.05 and a two-tailed comparison of means, a sample size of 176 PwP for each group would be sufficient to achieve a power of 0.80. In total, a case number of 352 PwP is needed due to the 1:1 matching. Considering a loss to follow-up in the intervention arm (estimated at 5%) [2], a total of 185 PwP needs to be initially included. PwP in the control groups will be surveyed via dPV. One study has been identified that recruited PwP via dPV with a resulting response rate of approximately 11% [12]. Considering a similar response rate of 11% for the ParkinsonAKTIV study and dPV’s current approximately 19,000 members across Germany, the inclusion of 185 PwP in the control arm appears to be reachable.

*Primary outcome* The primary outcome is health-related quality of life, assessed using the Parkinson’s Disease Questionnaire (PDQ-39, [1]). The PDQ-39 consists of 39 questions, subdivided into eight dimensions including items on symptoms, opportunities to participate, mobility and interferences in activities of daily living. Each question can be answered with following categories: “never” (= 0 points), “rarely” (= 1 point),” sometimes” (= 2 points), “often” (= 3 points) and “always” (= 4 points). A higher score indicates a reduction in quality of life (PDQ-39, [1]).

*Secondary outcomes. * The severity of PD symptoms will be assessed using the UPDRS, which evaluates various aspects of PD [5]. This instrument includes four different categories containing Part I: Non-Motor Aspects of Experiences of Daily Living, Part II: Motor Aspects of Experiences of Daily Living, Part III: Motor Examination and Part IV: Motor Complications. The questionnaire will be conducted during an interview with the respective patient by the treating neurologist. The UPDRS total score ranges from 0 to 199 points. A higher score indicates a physical or cognitive impairment of PwP [5].

The symptom progression of PD will be assessed by the treating neurologist using the Hoehn and Yahr scale [7], which comprises eight different disease stages. A higher disease stage indicates a higher limitation due to the PD [9].

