The severity of PD and activities of daily living will be assessed using the PD-specific Schwab and England Activities of Daily Living scale [14] by the treating neurologist. This scale rates the functional status of patients with PD on a scale from 0, indicating worst possible function, to 100, indicating no impairment.

Healthcare service utilization will be measured using the generic Questionnaire for Health-Related Resource Use in an Elderly Population (FIMA) [15]. It contains 28 questions that consider the patients’ utilization and healthcare costs of outpatient and inpatient treatments, medications, and other treatment procedures, such as physical therapy.

*Health economic evaluation* The health economic evaluation will be performed as a cost-effectiveness analysis considering total costs (direct and indirect costs) collected from patients via FIMA and quality of life as effect measures collected via PDQ-39. In addition, a cost analysis from a payer’s perspective will be performed using routine data from a statutory health insurance.

*Data analysis* Descriptive and associated analyses will be conducted to determine sample characteristics and provide summaries of outcome measures.

The primary and secondary outcomes will be evaluated according to the intention-to-treat principle. To test the robustness of the data, per-protocol analysis with complete cases only will be performed.

For the analysis of the primary outcome measure, PD-specific quality of life, all 39 items will be grouped into eight index scores, which then represent a percentage value between 0 and 100 (100 = many health problems). In a next step, linear models will be used to examine the difference in primary outcome between groups and will be reported as gain in quality of life within the 12-monthts observation period, with a 95% confidence interval. Sensitivity analyses will be conducted using multiple regression analysis, considering covariates such as age, gender, or duration of PD.

Secondary outcomes will be analyzed with dependent t-tests, to compare for potential differences in the intervention group within the course of the study (12 months).

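### The sample size and the paired t-tests make no allowance for intervention patients being nested within their treating neurologists

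*Protocol article*

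**What the plan says.** The sample size paragraph under *Effectiveness evaluation* describes the calculation as "According to a-priori power calculation, based on an independent t-test" with an "effect size of d = 0.3". The test level is given by "With an alpha of 0.05 and a two-tailed comparison of means", and the result is "a sample size of 176 PwP for each group would be sufficient to achieve a power of 0.80". The total follows from the matching ("a case number of 352 PwP is needed due to the 1:1 matching"). The only inflation is for 5% loss to follow-up, giving 185. No ICC, cluster size or design effect appears.

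On delivery, the same section states: "Recruitment of PwP takes place during face-to-face consultations by their treating neurologists". *Use of JamesAKTIV* has the neurologist open the patient's case, document the therapy prescribed and settle it with the therapist. The UPDRS, Hoehn and Yahr, and Schwab and England ratings are also made by the treating neurologist. Controls are individuals who respond through the patient association's journal.

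The only provider count is under *Process evaluation*: "Participants for the process evaluation are healthcare professionals located in the region of Muensterland, Tecklenburger Land and Osnabrueck, Germany", followed by 30 neurologists and 150 therapists.

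For the primary analysis, "linear models will be used to examine the difference in primary outcome between groups". Secondary outcomes are to be compared over 12 months within the intervention group by dependent t-tests. The incremental cost-effectiveness ratio (ICER) is to be bootstrapped with 5,000 replications. No cluster term or resampling unit is stated for any of these.

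**The concern.** Patients of one neurologist share that neurologist's prescribing, therapist contacts and uptake of the platform. The *Perspective* section itself describes a complex network intervention and says that getting professionals to adopt the new workflow is often a hurdle. Outcomes may therefore be more alike within a neurologist than between neurologists. In that case 176 intervention patients carry less information than 176 independent ones, and a test that counts them as independent uses too small a standard error.

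Controls are not grouped by provider in the design, so the extra variance falls in one arm only. At stake are the width of the 95% confidence interval for the primary effect, the error rate of the paired secondary tests and the stated power of 0.80.

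**Working it through.** **Inputs from the article:** d = 0.3 (so SD = 1), two-sided alpha 0.05, 176 evaluable patients per group, power 0.80.

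**Assumptions not in the article:** all 30 neurologists named for the process evaluation enrol patients; ICC 0.02, 0.05 or 0.10; caseloads either equal or with CV 1.0. For the paired tests, the ICC is that of 12-month change.

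**Step 1: reproduce the plan's figure.** Under independence SE0 = sqrt(1/176 + 1/176) = 0.1066. Power = Φ(0.3/0.1066 − 1.96) = Φ(0.854) = 0.804; the exact t-test gives 0.801. The exact calculation needs 175.4, so 176 per group. The stated figure is correct, and it reproduces with no allowance for clustering.

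**Step 2: design effect in the intervention arm only.** Mean cluster size m = 176/30 = 5.87.
- Equal caseloads: DE = 1 + (m − 1) × ICC. At ICC 0.05: 1 + 4.87 × 0.05 = 1.243.
- Unequal caseloads: DE = 1 + ((1 + CV²)m − 1) × ICC. At CV 1.0 and ICC 0.05: 1 + 10.73 × 0.05 = 1.537.

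**Step 3: power and type I error of the between-group comparison.** SE = sqrt(DE/176 + 1/176); power = Φ(0.3/SE − 1.96); type I error of a test that ignores clustering = 2[1 − Φ(1.96 × SE0/SE)].

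At ICC 0.05 with equal caseloads, SE = sqrt(2.243/176) = 0.1129. Power is Φ(2.657 − 1.96) = 0.757, and type I error is 2[1 − Φ(1.96 × 0.944)] = 6.4%.

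| ICC | DE, equal | Power | Type I error | DE, CV 1.0 | Power | Type I error |
|---|---|---|---|---|---|---|
| 0.02 | 1.10 | 0.785 | 5.6% | 1.215 | 0.763 | 6.3% |
| 0.05 | 1.24 | 0.757 | 6.4% | 1.537 | 0.705 | 8.2% |
| 0.10 | 1.49 | 0.714 | 7.9% | 2.073 | 0.622 | 11.4% |

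At ICC 0.01 with equal caseloads, power is 0.794. Allowing for the limited number of clusters in the degrees of freedom lowers the equal-caseload powers slightly, to 0.776, 0.748 and 0.703.

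**Step 4: paired tests in the intervention arm.** No unclustered arm dilutes the effect here, so type I error = 2[1 − Φ(1.96/sqrt(DE))]. With equal caseloads this is 6.1%, 7.9% and 10.8% at ICC 0.02, 0.05 and 0.10.

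**Step 5: sensitivity to the number of enrolling neurologists.** If only 15 enrol, with equal caseloads, m = 11.73 and power is 0.763, 0.705 and 0.622.

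**Step 6: size needed for 0.80.** With 30 neurologists and equal caseloads, the evaluable number per arm is 184, 199 and 234 (normal approximation), against 176 planned.

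**The case against.** Much of the case on the other side limits how far the point goes.

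- **The primary model and the bootstrap.** A reader might infer that these ignore clustering. The article does not show that. Linear models can carry a random intercept or cluster-robust errors, no resampling unit is named for the bootstrap, and an article may leave both to an analysis plan that is not shown. Here one can say only that no cluster term is stated.
- **Thirty neurologists for 185 patients.** A reader might take this as the plan's own figure. It is not: 30 is the process-evaluation count, and the number who enrol patients is not given. The 5.9 per neurologist is a division made for this review.
- **Actual power.** A reader might conclude that true power is below 0.80. That is not established. The article gives no ICC. The primary result is reported as a gain over 12 months, and the t-test calculation takes no credit for matching or for correlation with baseline, either of which could offset some of the loss.
- **Neurologist-rated scales.** A reader might suppose that these suffer most. A rater's constant leniency or severity cancels in a within-patient difference if the same neurologist rates both visits. Only neurologist-level variation in change remains, and its size is unknown.

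Two elements are nevertheless fixed in the article itself. The power of 0.80 is stated under independence, and no later analysis plan can make that calculation allow for nesting. A dependent t-test has no place for a cluster term.

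**Conclusion.** The point holds in a limited form. The sample size and the dependent t-tests make no allowance for nesting within treating neurologists, in a design where only the intervention arm is nested. The direction is certain for any positive ICC, other things equal: standard errors too small and stated power too high.

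The magnitude is conditional. With 30 equally enrolling neurologists, the loss of power is under 2 points at ICC 0.02 or below, which is negligible. It reaches about 5 points at ICC 0.05 and 9 at ICC 0.10. Uneven caseloads or fewer enrolling neurologists make it larger, with power down to 0.62 at ICC 0.10 in the cases tabulated. Confidence is high on the mechanism and moderate on the size. The change should be made, because it is cheap and the confidence interval for the primary effect depends on it.

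**What to change.** - **Primary outcome:** state a linear model with a random intercept for neurologist in the intervention arm only, controls entered as singletons, and small-sample degrees of freedom. Cluster-robust standard errors with a small-sample correction are an acceptable alternative.
- **Secondary outcomes:** replace the dependent t-tests with the equivalent clustered model of within-patient change.
- **ICER bootstrap:** resample neurologists in the intervention arm and individuals in the control arm.
- **Power:** keep 0.80 as the value under independence. Beside it give a range of about 0.71 to 0.79 with equal caseloads and 0.62 to 0.76 with uneven ones (CV 1.0), for ICC 0.02 to 0.10. Label the range with the assumed ICC, caseload CV and number of enrolling neurologists.

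The cost is a less favourable power figure and a neurologist identifier on each intervention record. The platform case is created by the neurologist, but the PDQ-39 and FIMA are paper surveys, so each must be linked to the patient's neurologist. No new outcome data are needed.

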^a^Only assessed in the intervention group

This study is registered at ClinicalTrials.gov (registration number NCT05251298). Ethical approval has been given by the ethics committee of the Medical Association Westphalia-Lippe and the University of Muenster (approval number: 2021-356-f-S).

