### The intervention: development of the online platform JamesAKTIV

An essential part of the ParkinsonAKTIV study is the development and use of the online platform called JamesAKTIV. Various professions, such as neurologists, physiotherapists, occupational therapists, speech and language pathologists, PD nurses, representatives of a German statutory health insurance, and IT specialists were involved in the development of JamesAKTIV. One major feature of JamesAKTIV is the digital quickcard for each patient which aims to establish guideline-based non-pharmacological therapy recommendations and to enhance structured communication between health professionals involved in care for patients with PD. The development process of quickcards is described in detail elsewhere [8].

JamesAKTIV contains the following features:Quickcards that can be filled out and shared between neurologists and therapists.A comments function for quick exchange of relevant information.A download section to access assessment forms.Individual patient accounts for therapy information and administration.A video section explaining the ParkinsonAKTIV project in detail.Educational videos for specific therapeutic interventions.

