### Study setting and training of staff

The intervention takes place in a specified area in the northwest of Germany (Muensterland and Osnabrueck). In this area, two multidisciplinary voluntary care networks of PD healthcare professionals exist, namely the PNM+ and the Parkinson’s Network Osnabrueck+(PNO+). Participating therapists and neurologists were recruited via these regional networks as well as from outside the networks in the region. All professionals participating in ParkinsonAKTIV are required to complete a 2-h education course on the use of JamesAKTIV. Moreover, all professionals working in ParkinsonAKTIV have had training on the use of quickcards and on diagnostics as well as treatment options in PD.

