Cost-effectiveness will be analyzed using an incremental cost-effectiveness ratio (ICER). The ICER measures the additional cost per unit of health gain and compares the differences between the intervention arm (specified as ‘i’ in the formula) and control arm (specified as ‘c’ in the formula) in terms of the mean total costs in the numerator and mean effects in the denominator:$${\text{ICER}} = {{\left( {{\text{costs}}_{{\text{i}}} - {\text{costs}}_{{\text{c}}} } \right)} \mathord{\left/ {\vphantom {{\left( {{\text{costs}}_{{\text{i}}} - {\text{costs}}_{{\text{i}}} } \right)} {\left( {{\text{effects}}_{{\text{i}}} - {\text{effects}}_{{\text{i}}} } \right)}}} \right. \kern-0pt} {\left( {{\text{effects}}_{{\text{i}}} - {\text{effects}}_{{\text{c}}} } \right)}}$$

To address uncertainties in the cost-effectiveness analysis, cost-effectiveness planes will be plotted based on a non-parametric bootstrapping method with 5.000 bootstrap replications. Furthermore, a cost-effectiveness acceptability curve (CEAC) will be constructed and univariate sensitivity analyses will be performed.

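### As written, the ICER numerator contains only patient-reported FIMA costs, so the programme's own cost is left out of the intervention arm

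*Protocol article*

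**What the plan says.** All of this is in the protocol article.

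- **Cost source.** Effectiveness evaluation, paragraph on the health economic evaluation: the cost-effectiveness analysis is performed "considering total costs (direct and indirect costs) collected from patients via FIMA and quality of life as effect measures collected via PDQ-39".
- **What FIMA covers.** Effectiveness evaluation, secondary outcomes: 28 questions on the patient's "utilization and healthcare costs of outpatient and inpatient treatments, medications, and other treatment procedures, such as physical therapy".
- **Other cost source.** The health economic paragraph continues: "In addition, a cost analysis from a payer’s perspective will be performed using routine data from a statutory health insurance".
- **The ratio.** Effectiveness evaluation, data analysis: "The ICER measures the additional cost per unit of health gain", comparing the arms "in terms of the mean total costs in the numerator and mean effects in the denominator". Uncertainty is handled by 5,000 bootstrap replications, cost-effectiveness planes, an acceptability curve (CEAC) and univariate sensitivity analyses whose parameters are not named.
- **What the intervention consumes.** The section on the intervention: "An essential part of the ParkinsonAKTIV study is the development and use of the online platform called JamesAKTIV". Study setting and training of staff: "All professionals participating in ParkinsonAKTIV are required to complete" a 2-hour course; training on quickcards and on PD diagnostics and treatment, of unstated length, comes on top. Use of JamesAKTIV: neurologists open cases and document prescriptions, therapists document the therapy, the two settle a joint decision, and the neurologist can monitor progress.

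**The concern.** The ICER is meant to price ParkinsonAKTIV against usual care. ParkinsonAKTIV is a platform plus coordinated professional work, and the resources that make it up are the ones a patient questionnaire cannot see. Controls receive treatment as usual, so the omission falls on one arm and does not cancel in the difference. The planned uncertainty work would not reveal it: the bootstrap resamples recorded costs, and a cost that was never recorded is missing from every replicate. The article presents cost-effectiveness as a strength of the design and the study as a roadmap for routine care. A payer would therefore be reading an ICER for the programme that leaves the programme out.

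**Working it through.** **Plan's own figures.** The article states no cost and no ICER, so there is nothing to reproduce on the disputed quantity. The one figure borrowed below is the intervention-arm size of 185. It follows from 176 per group and 5% loss: 176 / 0.95 = 185.3.

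**Step 1. Trace each resource to the numerator.**

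| Resource | Described under | Reaches the ICER as written? |
|---|---|---|
| Outpatient and inpatient care, medication, therapies (including extra therapy prompted by the programme) | Secondary outcomes (FIMA) | Yes, both arms |
| Insurer routine data | Health economic evaluation | No, separate payer analysis |
| JamesAKTIV development and operation | The intervention | No |
| Training of professionals | Study setting and training of staff | No |
| Quickcard and coordination time | Use of JamesAKTIV | No |

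**Step 2. Effect on the ratio.** Let C be the mean programme cost per intervention patient, F the mean FIMA cost and ΔE the difference in effects.

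- Planned incremental cost: F_i − F_c.
- Full incremental cost: (F_i + C) − F_c = (F_i − F_c) + C.
- Understatement: exactly C. With a positive gain ΔE, the ICER is too low by C / ΔE. (A higher PDQ-39 score is worse, so the gain is the reduction in score.)
- On the plane, the cloud of bootstrap points sits too low by C.
- For the CEAC at willingness to pay λ, the plan computes P(λΔE − ΔF > 0), where ΔF = F_i − F_c. The full version is P(λΔE − ΔF − C > 0). For C > 0 the planned curve is never below the full one.

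**Step 3. The part the article lets us count.**

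- Professionals (Process evaluation, recruitment): 30 + 150 = 180.
- Course hours: 180 × 2 h = 360 h.
- Per intervention patient: 360 / 185 = 1.95 h.

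**Step 4. Illustration in euros (assumptions, not document figures).**

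- At an assumed EUR 30 to 100 per hour: 360 × 30 / 185 = EUR 58 and 360 × 100 / 185 = EUR 195 per patient.
- This charges all one-off training to 185 patients. Spread over ten times as many (1,850), it is EUR 6 to 19.
- Platform: an assumed EUR 50,000 to 1,000,000 charged wholly to 185 patients is EUR 270 to 5,405 per patient.
- With the plan's d = 0.3 and an assumed PDQ-39 standard deviation of 10 to 20, ΔE is 3 to 6 points. C = EUR 58 to 195 then shifts the ICER by 58 / 6 = about EUR 10 to 195 / 3 = EUR 65 per point. C = EUR 1,000 shifts it by 1,000 / 6 = EUR 167 to 1,000 / 3 = EUR 333 per point.

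The range is wide because the article contains no cost inputs. The sign of the understatement does not depend on any of these assumptions.

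**The case against.** **An article condenses.** The health economics fills a few sentences. Micro-costing of platform, training and staff time is the kind of detail a full protocol or analysis plan supplies. The text does not say that FIMA is the only source, and the sensitivity analyses are left open. This stands in part: the full documents may add programme costs, and the article cannot show that they will not. But the article is not silent on the cost source. It specifies total costs as those collected from patients via FIMA and gives routine data a different job, so the rule as published omits the programme.

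**Downstream costs are counted.** This stands. FIMA picks up the extra therapy the programme is meant to generate. The gap is confined to platform, training and professional time.

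**Materiality is not shown.** This stands. There is no total cost to compare C with, the hourly rates are assumed, and charging all training to the trial patients is an upper allocation when the stated aim is routine care.

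**A stronger reading on timing.** Table 1 shows FIMA at t2 with the footnote "Only assessed in the intervention group", and a reader might infer that the 12-month totals would be built from three forms in one arm and two in the other. The documents do not support that. Nowhere does the article say that forms are summed or that t2 enters the between-arm comparison, and both arms share the baseline and 12-month forms. It is not an error in the plan.

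**Conclusion.** The point holds as a defect in the published cost rule. Followed as written, the ICER omits the programme cost, and the incremental cost is understated by C per intervention patient. For this component the direction is certain for any C > 0: it favours ParkinsonAKTIV. The only part that can be counted from the article is 360 hours of compulsory course time. Its value in euros, the total C and whether C matters against annual costs per patient cannot be determined.

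A reader might go further and infer that the final ICER is biased in the programme's favour. That does not follow. Controls are non-randomised respondents from a patient association, and differences between them and the intervention patients could move both costs and effects in either direction. The verdict also assumes that no unshown document already adds programme costs. The primary outcome analysis is not affected.

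**What to change.** Define intervention-arm costs as FIMA costs plus programme cost per patient, where programme cost covers platform operation, training hours and professional time for documentation and coordination. Take the amounts from project accounts and platform logs, and count only professional time that FIMA-recorded contacts do not already cover. Use the planned univariate sensitivity analyses to vary development cost and the number of patients over which one-off costs are spread. If programme costs are not to be added, state that the ICER excludes them and confine the conclusion to the change in patients' service costs per unit of quality of life.

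This costs analysis wording and some bookkeeping, with no new patient data. The downside is a less favourable ICER.

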### Use of JamesAKTIV

As illustrated in Fig. 1, treating neurologists log into JamesAKTIV and create a case for the PD patient under treatment. When the treating neurologist subscribes a non-pharmacological treatment, such as physiotherapy to their patient, he or she documents this treatment on JamesAKTIV as specific as possible. After an assessment by the therapist, a final decision is established between the neurologist and the therapist. Once the patient receives personalized treatment by a therapist, the kind of therapy (e.g., backpack training for camptocormia) is again documented in the quickcard by the physiotherapist and the progress, duration and the kind of therapy can be monitored by the treating neurologist.

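### The ICER takes its costs from patient-reported FIMA and names no source for the programme's own cost, so incremental cost is understated if the text is followed as written

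*Protocol article*

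**What the plan says.** All of this stands in the protocol article.

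- **Cost source.** Under Effectiveness evaluation, the Health economic evaluation paragraph describes a cost-effectiveness analysis "considering total costs (direct and indirect costs) collected from patients via FIMA", with PDQ-39 quality of life as the effect.
- **What FIMA measures.** The secondary outcomes text says: "It contains 28 questions that consider the patients’ utilization and healthcare costs of outpatient and inpatient treatments, medications, and other treatment procedures". It gives physical therapy as an example of the last group.
- **Where the costs go.** The ICER paragraph says: "The ICER measures the additional cost per unit of health gain". It compares the arms "in terms of the mean total costs in the numerator and mean effects in the denominator". Uncertainty is handled by 5,000 bootstrap replications, a cost-effectiveness plane, an acceptability curve (CEAC) and univariate sensitivity analyses whose parameters are not named.
- **Second cost source.** A further cost analysis from a payer's "perspective will be performed using routine data from a statutory health insurance". It is added to the cost-effectiveness analysis and does not feed the ICER.
- **Resources the programme uses.** Study setting and training of staff says: "All professionals participating in ParkinsonAKTIV are required to complete a 2-h education course on the use of JamesAKTIV". The same section mentions training on quickcards, diagnostics and treatment options, without hours. Process evaluation counts the professionals as "n = 30 neurologists and n = 150 therapists". Use of JamesAKTIV has the neurologist open a case and document the treatment, then reach a joint decision with the therapist. The therapy given is "again documented in the quickcard by the physiotherapist". The platform itself is described as an essential part of the study.

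**The concern.** An ICER for a care programme should carry the cost of the programme. Here the costs are called total, but their named source is a questionnaire on what patients themselves used. A patient can report a physiotherapy session. A patient cannot report that the physiotherapist attended a course, that the platform had to be hosted, or that two professionals exchanged entries on a quickcard between visits.

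These costs arise in the intervention arm only, so leaving them out is a systematic error with one sign on the cost side. Bootstrapping cannot reveal it, because resampling FIMA costs reproduces the same gap in every replicate. The article says its results will provide a roadmap for routine care. A reader deciding on routine care would see a cost difference without the price of what is being adopted.

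**Working it through.** **The plan's own figures.** The article gives no cost or ICER figure to reproduce. The sample size it states does reproduce: a two-sided t-test with d = 0.3, alpha 0.05 and power 0.80 needs 175.4 per group, hence 176. That figure does not bear on the point. The stated enrolment of 185 serves below as the number of intervention patients.

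**Direction.** Let ΔC and ΔE be the differences in mean cost and mean effect (intervention minus control). Let c be the programme cost per intervention patient that FIMA misses, and λ the willingness to pay per unit of effect.

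1. Cost difference with programme cost = ΔC + c. The control arm is unchanged.
2. Bootstrap: c is added to every intervention patient, so each replicate's cost difference rises by exactly c. As planned, each point on the plane sits c too low.
3. Net benefit with programme cost = λ·ΔE − (ΔC + c). As planned it is λ·ΔE − ΔC, too high by c at every λ.
4. CEAC: this is the share of replicates with positive net benefit. Subtracting c from each can only lower that share or leave it unchanged.
5. ICER with programme cost = (ΔC + c)/ΔE. The planned ratio is too low by c/ΔE **if ΔE is positive**. A higher PDQ-39 score means worse quality of life, so on raw scores a benefit makes ΔE negative and adding c would lower the ratio. The Data analysis paragraph speaks of a gain in quality of life, which suggests a reversed sign, but the coding for the ICER is not stated.

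**Size, from the document.** Only the 2-hour course can be sized.

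- Professionals: 30 + 150 = 180 (Process evaluation).
- Course hours: 180 × 2 = 360.
- Per intervention patient: 360/185 = 1.95 h, or 360/176 = 2.05 h on the analysed number.
- The course is a one-off, so the share falls with a later caseload. Spread over twice as many patients, for illustration, it is 360/370 = 0.97 h.

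**Size in money, on assumptions the document does not give.** Assume 30 to 100 EUR per staff hour and a PDQ-39 standard deviation of 10 to 20 points.

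- Course cost per patient: 360 × 30/185 = 58 EUR to 360 × 100/185 = 195 EUR.
- Effect at d = 0.3: 0.3 × 10 = 3 points to 0.3 × 20 = 6 points.
- ICER shift from the course: 58.4/6 = 10 EUR to 194.6/3 = 65 EUR per point gained.
- Each further 100 EUR of programme cost per patient adds 100/6 = 17 to 100/3 = 33 EUR per point.

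Platform operation, the further training and the quickcard and coordination time come on top. The document gives nothing from which to size them.

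**The case against.** The strongest reply is that this is a condensed article. It covers the economic evaluation in a few sentences and never says that FIMA is the only source. Programme costing, unit prices and amortisation commonly sit in a fuller document that is not shown. The Abstract lists cost data next to patient-reported outcomes and routine data, which could mean more than patients report. The unnamed sensitivity analyses might include a programme cost.

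Part of this stands. A reader might infer that the plan deliberately excludes programme cost or sets it to zero, and the article does not say so. But it is not simply silent either. It calls the costs total, names where they come from, and assigns routine data to a separate analysis. Someone following that text would leave the programme out of the base case, whatever was varied afterwards.

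Three further objections stand and limit the point:

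- **Overlap.** Some quickcard and case-opening work may happen during consultations or therapy sessions that FIMA already counts. Extra sessions prompted by the programme are also in FIMA. Only what lies outside those visits is missing.
- **Money.** A reader might be tempted to put several hundred euros per patient on the gap by adding assumed minutes per quickcard entry. Nothing in the document supports such a figure.
- **Consequence.** No cost difference, cost spread or willingness-to-pay threshold is given, so it cannot be shown that a conclusion on cost-effectiveness would change.

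Insurer data might show programme costs if they are billed. The article does not say whether they are, and those data do not feed the ICER in any case.

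**Conclusion.** The point holds as a defect in how the ICER's costs are specified. Under the stated rule, incremental cost is understated by c, net benefit is overstated by c, and the acceptability curve can only err in the programme's favour. The claim that the ICER itself is too low needs one condition: effects coded so that a gain is positive, with a positive difference.

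The document alone supports a size of 360 course hours, about 1.95 per intervention patient if charged wholly to 185 patients. The range of 10 to 65 EUR per PDQ-39 point for the course rests on assumed hourly rates and an assumed standard deviation, and is an illustration.

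Severity is moderate. The primary PDQ-39 comparison and the sample size are untouched, and the gap can be closed in the analysis without changing any patient procedure.

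**What to change.** In the Health economic evaluation and ICER paragraphs:

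1. Define intervention-arm cost as FIMA cost plus a per-patient programme cost. Include training, platform operation, and quickcard and coordination time not already inside visits that FIMA counts, so that nothing is counted twice.
2. Add this cost to every intervention patient before the ICER, bootstrap and CEAC are computed.
3. Vary it in the univariate sensitivity analyses already planned, including the number of patients over which training is spread. Show platform development cost as a separate scenario.
4. State the perspective of the cost-effectiveness analysis.
5. State that the PDQ-39 effect is coded so that a gain is positive.

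The cost is a small costing exercise and a less favourable ICER. The article does not say that attendance records, platform invoices or quickcard counts are being kept, so their availability must be checked. The planned interviews cover acceptance, barriers and facilitators. If staff time is to be estimated there, a question has to be added.
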